### Intervention

2.8

#### EPN group

2.8.1

EPN consists of needles fixed on a sticky tape with a short and thin body, and a specially made electrical device charged by Li-Polymer battery of 3.7 V, through which a mixing microcurrent is output (Fig. 3). It will be administrated by officially licensed acupuncturists who have at least 2 year clinical experience in this trial.

Body acupoints of Yintang (GV29), Dazhui (GV14), Guanyuan (CV4), bilateral Zigong (EX-CA1), and bilateral Sanyinjiao (SP6) and auricular acupoints of Heart (CO15), Chuiqian (LO4), and Shenmen (TF4) will be selected in the treatment. Auricular acupoints on the right and left ear will be stimulated alternatively, 1 side each time. The location of the acupoints is determined based on the “Nomenclature and location of acupuncture points” drafted in 2006 and Nomenclature and Location of Auricular Points by the National Standard of the People's Republic of China (GB/T 12346–2006 and GB/T13734-2008). Detailed locations of the acupoints are displayed in Table 2 and Figure 2. Body acupoints will be stimulated by press needles 0.25 mm in diameter and 2 mm in length (ZhenXing Brand, Hangzhou Yuanli Medical Appliance Factory, China) and ear acupoints will be stimulated by press needles 0.25 mm in diameter and 0.9 mm in length (ZhenXing Brand, Hangzhou Yuanli Medical Appliance Factory, China).

**Table 2 T2:** Location of body and auricular acupoints in the trial.

Acupoints	Locations of the acupoints
Yintang (GV29)	The midpoint of the two brows
Dazhui (GV14)	Below the spinous process of the seventh cervical spine
Guanyuan (CV4)	Three inches below the navel
Zigong (EX-CA1)	Four inches below the navel and four inches beside it
Sanyinjiao (SP6)	posterior to the medial border of the tibia, three cun superior to the prominence of the medial malleolus
Heart (CO15)	In the middle depression of the ear concha cavity
Chuiqian (LO4)	Area four of the nine areas at the lower margin of the antilobium notch
Shenmen (TF4)	In the upper part of the posterior third of the triangle fossa, namely the triangle fossa four area

**Figure 2 F2:**
[figure not shown]
Acupoints diagram.

After sterilization of the local skin, the needle will be pressed to the acupoints and the tape will be sticked to the skin. Since the needles are very short and thin, patients will sense no pain during the administration. Then, the electric device (ϕ44 × 15.8 mm ZXHPAMDZB-02C) together with the electrode patch will be sticked to the surface of skin (on top of the sticky tapes of the press needle) in the area of CV4 and bilateral EX-CA1, and bilateral SP6 respectively (Fig. 3). The electrical device will be switched to the mode of “dense intermittent wave,” and the current intensity will be increased gradually till the muscles around jump slightly (within the tolerance of the participants).

**Figure 3 F3:**
[figure not shown]
EPN and electrical device. EPN = electro-press needle.

The treatment session in the clinic will last for 40 minutes each time. All needles on the body acupoints will be removed after each session, while those on the auricular acupoints can be kept for as long as 6 hours (removed before patients going to bed). The needles on the ear will be pressed by hand vertically for 1 minute every 2 hours to reach the gentle sensation of soreness and pain. Patients will be treated for 6 weeks, 3 sessions per week, and 18 sessions in total.

#### Waitlist control group

2.8.2

Patients in the waitlist control group will receive no intervention for the first 6 weeks and be followed up in the next 24 weeks. If the HF symptom of the patients in the wait list does not heal itself, 6 weeks of EPN therapy will be offered to the patients as a compensation.

#### Outcome measurements

2.8.3

##### Primary outcome measure

2.8.3.1

The primary outcome is the proportion of patients with a reduction of 50%^[17]^ or more on the mean 24-hour HF score from baseline at week 6.

Participants will record the frequency and severity (mild, moderate, severe, and very severe) of each HF in 7-day HF diary (HFD). It was a feasible and acceptable tool for women to complete over 7 days with minimal missing data.^[14,15]^ HF score will be calculated based on the frequency and severity of each HF recorded in 7-day HFD to evaluate the severity of general symptoms, as follows: mean 24-hour HF score = (1 × number of mild HF + 2 × number of moderate HF + 3 × number of severe HF + 4 × number of very severe HF)/Number of days reported.

##### Secondary outcome measure

2.8.3.2

1.The proportion of patients with a reduction of 50%^[17]^ or more on the mean 24-hour HF score from baseline at weeks 3, 18, and 30.2.The proportion of patients with a reduction of 50% or more on the mean 24-hour HF frequency from baseline at weeks 3, 6, 18, and 30. The mean 24-hour HF frequency will be calculated based on the number of HF recorded in 7-day HFD, as follows: mean 24-hour HF frequency = total number of HF reported/number of days reported.3.The proportion of patients with at least a 50% reduction in the mean 24-hour HF severity from baseline at weeks 3, 6, 18, and 30. The mean 24-hour HF severity will be calculated based on the frequency of HF and the severity of each HF recorded in 7-day HFD, as follows: mean 24-hour HF severity = (1 × number of mild HF + 2 × number of moderate HF + 3 × number of severe HF + 4 × number of very severe HF)/number of HF reported.4.The changes in the mean 24-hours HF score^[17]^ from baseline at weeks 3, 6, 18, and 30. A decrease of 5.35 episodes in moderate and severe HF per day from baseline has been reported as minimal clinically important difference (MCID).^[18]^5.The changes of MRS score from baseline at weeks 6, 18, and 30. MRS is a menopause-specific subscale commonly used for Chinese women. It includes 11 items concerning psychological, somatic, and urogenital domains.^[19]^ The scores of MRS range from 0 (best) to 44 (worst), and an increase of 5 points is regarded as the MCID).^[20]^6.The changes of MENQOL score from baseline at weeks 6, 18, and 30. MENQOL is a validated measurement of the quality of life and clinical symptom changes during the menopausal transition and the first 8 years postmenopause.^[21]^ It consists of 29 items to assess the 4 domains of vasomotor symptoms, physical symptoms, psychological symptoms, and urogenital/sexual symptoms. The total score of MENQOL ranges from 0 (best) to 174 (worst), with a reduction of 4 points as MCID.^[21–22]^7.The proportion of participants reporting “significantly reduced” or “moderately reduced” based on Global Response Assessment at weeks 3, 6, 18, and 30. The responses of participants to the treatments are divided into 7 grades of Global Response Assessment: significantly reduced, moderately reduced, slightly reduced, no change, slightly aggravated, moderately aggravated, and significantly aggravated. The proportion of participants reporting “significantly reduced” or “moderately reduced” are recorded as the response rate of overall efficacy.8.Patients’ acceptability toward EPN at the end of the 1st and 9th treatments. The acceptability toward EPN will be assessed among participants in the EPN group using a 3-point index: unacceptable (0 points), acceptable (1 point), and easy to accept (2 points). Those who regard EPN unacceptable will report the reasons. The average score will be calculated after the 2 assessments.9.Expectations and confidence of patients in the EPN group at baseline. Patients in the EPN group will answer the following questions before the first intervention: “Do you think acupuncture is effective for treating the disease?” and “Do you think acupuncture is effective in alleviating menopausal associated HF?” The participants can answer “Yes,” “No,” or “Unclear.”

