### Inclusion criteria

2.6

Patients who fulfill all following criteria will be included.

1.Aged between 40 and 60 years old.2.Scoring 14 points or more^[13]^ in at least 1 day during the 1-week baseline assessment, or having an average of ≥ 7 moderate or severe heating per 24 hours^[8]^ recorded in HF Dairy.^[14,15]^3.Fulfilling either condition mentioned below:a.The last menstrual period was more than 12 months ago (including 12 months);b.In the late menopausal transition, and has amenorrhea for more than 60 days;c.Follicle-stimulating hormone ≥25IU, and has vasomotor symptoms of HF, sweating, insomnia, migraine, or restlessness, etc.4.Volunteer to participate in this study and sign the informed consent.

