### Statistical analysis

2.9

The primary outcome of 24-hour mean HF score will be compared between the EPN group and the waitlist control group at week 6. Those who did not feedback data of HF score at week 6 will be regarded as patients whose reduction does not reach 50%. A *P* value <.05 will be considered statistically significant. Subgroup analysis will be conducted among perimenopausal patients and postmenopausal patients.

Continuous data will be presented as mean ± standard deviation when normally distributed, or be presented as median (interquartile range) when not normally distributed. Categorical data will be presented as the number and percentage of participants. Statistical comparisons will be performed by Student *t* test or Wilcoxon rank sum test for continuous data and by X^2^-test or Fisher exact test for categorical data. Data will be analyzed using SPSS software V.22.0 (IBM SPSS Statistics; IBM Corp, Somers, NY).

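### Secondary outcome 3 applies a 50% responder cut to mean severity per hot flash, which cannot halve from a baseline below 2 while any hot flash remains and has no value when none remain

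*Protocol article*

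**What the plan says.** Section 2.8.3.2, item 3, defines the outcome as "The proportion of patients with at least a 50% reduction in the mean 24-hour HF severity from baseline", at weeks 3, 6, 18 and 30. The formula starts "mean 24-hour HF severity = (1 × number of mild HF + 2 × number of moderate HF" and ends "4 × number of very severe HF)/number of HF reported". The denominator is therefore a count of episodes. The HF score (section 2.8.3.1) and the HF frequency (section 2.8.3.2, item 2) are instead divided by the number of diary days reported.

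The diary described in section 2.8.3.1 has four grades, from mild to very severe, and no zero grade.

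Section 2.6 offers two symptom routes into the trial. One is "Scoring 14 points or more" on at least one baseline day. The other is "having an average of ≥ 7 moderate or severe heating per 24 hours". Neither sets a lower limit on average severity per episode, and neither limits additional mild HF.

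The one related data rule, in section 2.9, is "Those who did not feedback data of HF score at week 6 will be regarded as patients whose reduction does not reach 50" per cent. It concerns an HF score that was not supplied at week 6. It does not cover a diary that was returned and shows no HF.

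**The concern.** A 50% responder cut suits a measure that can fall to zero. Score and frequency can, because a week without HF gives 0 divided by the days reported. Mean severity per HF cannot: its lowest value is 1 while one episode remains, and with no episodes it has no value. The same cut therefore asks different things of different women. From a baseline of 4 there is ample room to halve. From exactly 2, every remaining HF must be mild. Below 2, only complete disappearance could count, and that is the case in which the formula breaks down.

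At stake is whether the responder proportions at weeks 3, 6, 18 and 30 can be interpreted. They would reflect the baseline mix of severity, and a coding choice for symptom-free women, as well as any change in the intensity of HF.

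**Working it through.** The article gives no expected value for this outcome, so there is no planned figure to reproduce. The sample size in section 2.8.3.4 rests on the score responder rate (55% against 28%) and does not use item 3.

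**Inputs.** Weights 1, 2, 3, 4 and division by number of HF (section 2.8.3.2, item 3); four grades, no zero (section 2.8.3.1); threshold of 50% (item 3); entry routes (section 2.6).

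**Step 1: bounds.** With a, b, c, d the numbers of mild, moderate, severe and very severe HF, S = (a + 2b + 3c + 4d)/(a + b + c + d). If at least one HF is present, the minimum is 1 (all mild) and the maximum is 4 (all very severe).

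**Step 2: largest reduction while any HF remains.** The best follow-up value is 1, so the largest reduction is 1 − 1/S. It reaches 50% only if S/2 ≥ 1, that is S ≥ 2.

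| Baseline S | Value needed (S/2) | Largest reduction | 50% reachable with HF remaining? |
|---|---|---|---|
| 1.0 | 0.50 | 0% | no |
| 1.5 | 0.75 | 33.3% | no |
| 1.7 | 0.85 | 41.2% | no |
| 1.9 | 0.95 | 47.4% | no |
| 2.0 | 1.00 | 50.0% | only if every remaining HF is mild |
| 2.5 | 1.25 | 60.0% | yes |
| 3.0 | 1.50 | 66.7% | yes |
| 4.0 | 2.00 | 75.0% | yes |

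**Step 3: can women with S below 2 enter?** These illustrative daily patterns meet section 2.6:

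- 7 moderate + 1 mild: S = (14 + 1)/8 = 1.875; maximum reduction 46.7%.
- 7 moderate + 3 mild: S = (14 + 3)/10 = 1.70; maximum 41.2%.
- 2 severe + 5 moderate + 6 mild: S = (6 + 10 + 6)/13 = 1.69; maximum 40.9%.
- 14 mild on a single day: score 14, S = 1.00 for that day. This is a boundary case, since her weekly S also depends on the other days.

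**Step 4: what the floor does.** Take the woman with 7 moderate + 3 mild per day and let her fall to 1 mild HF per day, the best severity value the formula allows. Her score falls from 17 to 1, a reduction of 1 − 1/17 = 94.1%. Her severity falls from 1.70 to 1, a reduction of 41.2%. She is a responder on score and a non-responder on severity.

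**Step 5: no HF in the diary week.** Numerator and denominator are both 0, so S is undefined. In an arm with n women, let z have no HF and let r of the others meet the cut. The responder rate is r/(n − z) if the z women are left out, r/n if they count as failures, and (r + z)/n if they are set to 0 and so count as responders. The article does not choose among these.

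**The case against.** The strongest reply accepts the algebra and disputes how far it reaches. Four stronger readings are tempting, and the document does not support them.

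- **That a woman with baseline below 2 can never respond.** This holds only while some HF remain. If a symptom-free week were scored 0, she could respond by complete resolution. The reply stands, and the point is limited accordingly.
- **That complete responders are left out.** The article does not say so. Coding a zero denominator is a detail that an analysis plan may settle, and counting these women as responders is equally open. This stands too. Such a rule would not, however, remove the floor at 1 for women who still have HF, and that floor follows from a formula and a threshold which the article itself fixes.
- **That the outcome fails because a fall from 14 to 1 moderate HF per day scores 0% on severity.** That is a per-episode measure working as intended, since intensity did not change. The gain is captured by score and frequency. The example in step 4 differs: intensity did fall, as far as the scale permits, and still cannot count.
- **That the group difference is pushed toward zero at all four visits.** The floor acts in both arms, the coding of symptom-free women is unknown, and the share with baseline below 2 is not given. At weeks 18 and 30 the waitlist arm may also have had EPN, offered from week 7, which affects those contrasts whatever the formula.

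It is also fair to say that the trial describes its population as having moderate to severe HF, so baselines below 2 may be uncommon. The document does not show either way.

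**Conclusion.** The point holds as a moderate one, confined to a secondary outcome. It is certain, from the article's own formula, that a 50% reduction in mean severity per HF is out of reach from any baseline below 2 while HF remain, that the entry criteria permit such baselines, and that the article gives no value for a diary without HF. The responder rate therefore depends on baseline severity and on an unstated choice.

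The baseline patterns used are illustrations, not estimates of how many women have them. Without the share below 2 and the coding rule, neither the size nor the direction of the effect on the group difference can be computed. The primary outcome, its rule for missing week 6 data and the sample size are untouched.

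The 24-hour label is a lesser matter. It is inaccurate, because the measure is per episode, but the explicit formula leaves no doubt about the calculation.

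**What to change.** Drop the 50% cut for severity. Analyse the change in mean severity per HF as a continuous outcome, adjusted for baseline, among women with at least one HF in the diary week. Report beside it the proportion with no HF in each arm.

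If one measure for all women is wanted, prespecify severity = 0 for a returned diary that shows no HF. Compare the arms with a rank-based test, because the scale then jumps from 1 to 0. Section 2.9 already lists the Wilcoxon rank sum test.

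In either case, rename the measure *mean severity per HF* and keep the 50% cuts for score and frequency, where they work. Settle the choice before results by arm are seen.

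The cost is a change of wording, with the same diary data. There are two small losses: severity is no longer reported as a responder proportion, and the analysis of women who still have HF is conditional on a state reached after randomisation. The proportion with no HF is reported alongside for that second reason.

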A clinical study published in 2016 revealed no statistically important difference between acupuncture and sham acupuncture (noninsertion acupuncture using blunt-tip needles) in reducing HF scores of menopausal women.^[8]^ Our previous multicenter randomized trial, conducted among 360 (180/180) women during menopause transition, indicated that the difference between the electroacupuncture group and sham electroacupuncture (minimal acupuncture at nonacupoints) was as modest as 1.2 (95% CI: 0.6–1.8, *P* = .001) in the reduction of mean 24-hours HF score after 8-week treatment.^[9]^ Nevertheless, in both of these 2 trials, the HF score reduced significantly from baseline after treatment in either acupuncture group or sham acupuncture group (reaching or approaching the clinically important difference). This controversy may arise from the following 2 reasons. First, as an integrated therapy, the effectiveness of acupuncture might be partially accounted by the placebo effects, which is especially true when treating menopause symptoms.^[10]^ Notably, the placebo effects of sham acupuncture are reported to be stronger than that of a placebo tablet.^[11]^ Second, sham acupuncture is hard to act as an inert control because either tiny acupuncture or noninsertion acupuncture using blunt-tip needles may produce certain biological effects.^[7,12]^

To clarify the controversy whether acupuncture works in treating perimenopausal and postmenopausal HF or not, this randomized controlled trial is designed to compare acupuncture intervention group against the nonintervention group. Electro Press Needle (EPN), a novel acupuncture needle combining shallow and gentle insertion with transdermal electrical stimulation, will be used in the acupuncture intervention group.

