**Figure 1 F1:**
[figure not shown]
Flow chart of participants through the proposed trial. ∗ The Waitlist control group can receive 6 weeks EPN therapy as compensatory at weeks 7.

**Table 1 T1:** Outcome assessment schedule.

		Intervention		Follow-up	
Timepoint	Enrollment and allocation baseline week -1-0	Week 3	Week 6	Week 18	Week 30
HF dairy	X	X	X	X	X
MRS	X		X	X	X
MENQOL	X		X	X	X
Global response assessment		X	X	X	
Acceptability evaluation	X	X			
Expectance and confidence evaluation			X		
Safety evaluation of EPN			X		
Adverse events			X		
Combination of medication			X		
Adherence evaluation			X		
Completeness of research			X		

EPN = electro-press needle, HF = hot flashes, MENQOL = menopause-specific quality of life questionnaire, MRS = menopause rating scale.

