### Recruitment strategies

2.2

Patients are planned to be recruited via advertisements in websites and posters from hospitals and communities. All potentially eligible women with hot flashes will be invited to the trial, continued with a series of history taking, questionnaire, HF diary, ultrasound of uterus and ovaries, and laboratory examination to screen and enroll the patients, as recommended by ACOG guideline.^[2]^ Eligible patients will be randomly divided into EPN group and waitlist control group.

Personal information including age, marriage, menstrual, education background, and medical history are cautiously recorded. Hot flashes diaries are applied to assess the severity of HF symptoms. Menopause rating scale (MRS) and Menopause-Specific Quality of Life Questionnaire (MENQOL) are applied to assess the influence on the quality of life. Patients’ expectance and confidence evaluation toward EPN will also be evaluated before the trial. The duration of the trial is 31 weeks for each patient, including 1-week baseline assessment (week 0–1), 6-week treatment period (week 1–6), and 24-week follow-up (week 7–30).

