### Blinding

2.4

The acupuncturists and patients in this trial cannot be blinded. Evaluators and statisticians will be assigned separately from the operators to ensure they are blinded to the group allocation.

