##### Sample size calculation

2.8.3.4

The sample size was calculated based on the primary outcome, which is the proportion of participants with a reduction of 50% or more on their mean 24-hour HF score from baseline at week 6. The proportion of participants with at least a 50% decrease from baseline in 6 weeks was assumed to be 55% in the EPN group and 28% in the waitlist control group based on the previous research.^[9,23]^ Therefore, a sample size of 49 in each group is estimated to detect the group difference of 27%, with 80% power and a 2-sided significance level of 5%. A total of 122 patients (61 in each group) will be recruited for the study, assuming drop-off rate of 20% in the follow-up.

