The design of the trial has some limitations. First, neither the acupuncturist nor the patients are blinded, and the results may be biased to a certain extent, although a strict process of randomization and concealment will be performed to minimize the potential bias and outcome assessors and statisticians will be blinded, which is to avoid the evaluation bias. Second, there is a lack of placebo control in the study and the specific therapeutic effect of EPN cannot be assessed. We choice a waitlist group control to evaluate the effectiveness of acupuncture as a whole.

**Supplemental Content legends:** Supplemental Figure. Standard Protocol Items: Recommendations for Interventional Trials (SPIRIT)

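### The protocol contradicts itself on who answers the expectation and confidence questions and when; as item 9 is written they come from one arm only, and by implication after allocation

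*Protocol article*

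**What the plan says.** Three places in the protocol article deal with this measure.

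- **Section 2.8.3.2, item 9.** The outcome is titled "Expectations and confidence of patients in the EPN group at baseline", and the text specifies that "Patients in the EPN group will answer the following questions before the first intervention". Two questions follow, on whether acupuncture works for the disease and for menopausal hot flashes, each answered Yes, No or Unclear.
- **Section 2.2 (Recruitment strategies).** Alongside personal history, the diary, MRS and MENQOL, the protocol says that patients' "expectance and confidence evaluation toward EPN will also be evaluated before the trial". No arm is named.
- **Table 1.** The row "Expectance and confidence evaluation" carries a single mark. In the text at hand it falls under Week 6, but the columns may have shifted when the table was extracted.

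Section 2.4 adds that "The acupuncturists and patients in this trial cannot be blinded".

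**The concern.** Questions can be limited to the EPN group only once it is known who is in that group. Under item 9 the answers are therefore given after allocation, and because patients are not blinded, the women answering very probably know that they will be treated. Their answers may already reflect that knowledge, so calling them a baseline is misleading. The waitlist has no counterpart.

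This matters because the primary outcome is built from a diary that the patient fills in herself, so blinded evaluators do not shield it from expectation. The Introduction accepts that "the effectiveness of acupuncture might be partially accounted by the placebo effects, which is especially true when treating menopause symptoms". Waitlist beliefs could matter as well: section 2.8.2 offers EPN later to waitlist women whose symptoms persist, and item 9 would not record what those women believed.

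With data from one arm only, the trial could not show that the arms were alike in expectation, nor describe whether the between-arm difference varied with it. An association seen within the EPN arm alone could reflect prognosis, placebo response or reporting, with nothing to set it against.

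**Working it through.** **1. The passages side by side**

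| | Section 2.2 | Item 9 |
|---|---|---|
| Who | patients, no arm named | EPN group only |
| When | before the trial | before the first session |
| Relative to allocation | before it, on a plain reading | after it, implied by the one-arm restriction |
| Waitlist women asked | 61 of 61, if all are asked | 0 of 61 |

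Table 1 does not settle the matter. The mark's position is unreliable in the extracted text, and the first column combines enrolment, allocation and baseline. I give it no weight.

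**2. Does anything require one arm only?** Item 8 (acceptability of EPN) can be answered only by treated women. Item 9's two questions concern acupuncture in general and can be answered by any of the 122 women before allocation.

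**3. The plan's own sample size, as a check on the inputs.** Response is "assumed to be 55% in the EPN group and 28% in the waitlist control group", with two-sided 5% significance and 80% power. The unpooled normal formula gives

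n = (1.960 + 0.842)² × (0.55×0.45 + 0.28×0.72) / 0.27² = 7.849 × (0.2475 + 0.2016) / 0.0729 = 48.35, rounded up to 49 per group.

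This matches the plan. With 20% dropout, 49/0.8 = 61.25, against 61 stated. Asking a baseline question of more women changes none of this.

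**4. How much could an analysis by expectation show?** The split between Yes and No/Unclear is not in the documents, so it is assumed. Take 61 per arm, the planned response rates in both strata, the same split in each arm, and no dropout. For stratum sizes m₁ and m₂ per arm, the standard error of the difference between the two risk differences is

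SE = √[(0.2475 + 0.2016) × (1/m₁ + 1/m₂)].

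| Assumed split | m₁, m₂ | SE | 95% half-width (1.96 × SE) | Detectable at 80% power (2.80 × SE) |
|---|---|---|---|---|
| 50/50 | 30.5, 30.5 | 0.172 | ±34 points | 48 points |
| 80/20 | 48.8, 12.2 | 0.215 | ±42 points | 60 points |

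The planned overall effect is 27 points. An interaction would have to be roughly twice that size to be detected reliably.

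**The case against.** The strongest reply is that section 2.2 may govern. On that reading all women are asked before the trial, and item 9 only says which arm's answers are reported as an outcome. This stands in part. A reader might infer from item 9 that expectation is never measured in the waitlist arm, or in anyone before randomisation. The documents do not support that as a fact, because section 2.2 points the other way. That allocation is known when the questions are answered is likewise an inference from item 9, though a sound one, and not a statement in the text.

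A second reply is that the trial sets out to estimate acupuncture as a whole against no treatment. Expectation is then partly inside the contrast, and the Discussion concedes that "there is a lack of placebo control in the study and the specific therapeutic effect of EPN cannot be assessed". This also stands. A reader might call expectation the main rival explanation that the trial leaves unexamined; given the stated aim and the disclosed limitation, that goes too far. It does not, however, justify measuring expectation in one arm only once the decision to measure it has been made, and biased diary reporting is no part of the intended effect.

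Third, randomisation balances prior expectation up to chance, and a question asked beforehand cannot capture the effect of learning one's allocation. Both are correct. The primary comparison needs no adjustment for expectation, and symmetric measurement would not correct open-label bias.

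Finally, this is a descriptive item, last of nine secondary outcomes, and supportive analyses may be left to a fuller plan. That is a reason not to ask for a formal interaction test. It does not resolve two conflicting statements about who is asked and when.

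**Conclusion.** The protocol contradicts itself on who is asked and when, and the version in the outcome definition is the weaker one. Followed as written, item 9 gives expectation data from at most 61 of 122 women, all in one arm and, by implication, after allocation. Such data cannot show balance or be related to the between-arm difference. Section 2.2, read plainly, would give a symmetric pre-randomisation measure in all 122.

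The consequence is limited to interpretation. The primary outcome, its test and the sample size are not affected, and the documents give no figure for the size of any expectation effect. The precision figures of ±34 to ±42 points rest on the planned response rates, full follow-up and assumed splits. The point still merits a change before recruitment, because a pre-allocation answer cannot be obtained once the envelope has been opened.

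**What to change.** Reword item 9 so that all patients answer both questions during the 1-week baseline assessment, before the randomisation envelope is opened, in line with section 2.2. Align the Table 1 row with this. Report the answers by arm as a baseline characteristic.

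If the week-6 responder difference is shown by expectation (Yes versus No/Unclear), label it descriptive, give estimates with confidence intervals, and draw no conclusion from an interaction test. State that the measure describes expectation and does not correct for lack of blinding.

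The cost is two short questions for 61 more women at a visit they already attend, plus a row or two in the baseline table. No visits or staff are added.
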